## Abstract

**Background:**

Oxidative stress is associated with increased cardiovascular morbidity and mortality particularly in patients with end stage kidney disease. Although observational data from the general population has shown dietary antioxidant intake is associated with reduced cardiovascular morbidity and mortality, most clinical intervention trials have failed to support this relationship. This may be a consequence of not using an effective antioxidant dose and/or not investigating patients with elevated oxidative stress. The SPACE study, conducted in haemodialysis patients, reported that 800 IU/day of alpha tocopherol significantly reduced cardiovascular disease endpoints. A recent time course and dose response study conducted in hypercholesterolaemic patients that found 1600 IU/day of alpha tocopherol was an optimal dose. There is no such dose response data available for haemodialysis patients. Therefore the aim of this study is to investigate the effect of different doses of oral alpha tocopherol on oxidative stress in haemodialysis patients with elevated oxidative stress and the time taken to achieve this effect.

**Methods:**

The study will consist of a time-course followed by a dose response study. In the time course study 20 haemodialysis patients with elevated oxidative stress will take either 1600 IU/day natural (RRR) alpha tocopherol for 20 weeks or placebo. Blood will be collected every two weeks and analysed for a marker of oxidative stress (plasma F_2_-isoprostanes) and alpha tocopherol. The optimum time period to significantly decrease plasma F_2_-isoprostanes will be determined from this study. In the dose response study 60 patients will be randomised to receive either placebo, 100, 200, 400, 800 or 1600 IU/day of natural (RRR) alpha tocopherol for a time period determined from the time course study. Blood will be collected at baseline and every two weeks and analysed for plasma F_2_-isoprostanes and alpha tocopherol. It is hypothesised that doses ≥ 800 IU of vitamin E will be required to significantly decrease plasma F_2_-isoprostanes.

**Discussion:**

This study will determine the time and dose required for alpha tocopherol to significantly decrease oxidative stress in haemodialysis patients. Data will be used to plan a large randomised controlled trial to assess the effects of alpha tocopherol on cardiovascular outcomes in haemodialysis patients.

**Trial Registration:**

ACTRN12609000608268

## Background

Oxidative stress is an important contributor to the development of atherosclerosis and hence cardiovascular morbidity and mortality [1]. Observational studies suggest diets high in antioxidants such as alpha tocopherol may be associated with decreased cardiovascular disease [2,3]. However, antioxidant intervention trials have failed to demonstrate cardiovascular mortality benefits [4-11]. This may be due to the type and dose of antioxidant selected and the features of the populations studied. For example, trials have not selected elevated oxidative stress as an inclusion criteria therefore the study participants may not have been the most likely to benefit.

Chronic kidney disease is associated with high levels of oxidative stress, and treatment with haemodialysis can further increase oxidative stress levels, which may contribute to high level of cardiovascular disease in these patients [1,12]. These patients have a 10-20 times higher rate of cardiovascular disease morbidity and mortality compared to healthy people [13,14].

Alpha tocopherol is the main form of vitamin E and this has been the most commonly studied dietary antioxidant supplement in clinical trials. In one of the few trials to demonstrate a beneficial cardiovascular affect, the Secondary Prevention with Antioxidants of Cardiovascular disease in End stage renal disease (SPACE) study assessed the effects of 800 IU of alpha tocopherol on cardiovascular outcomes in 196 haemodialysis patients [15]. In this randomised controlled trial there was a significant reduction in cardiovascular disease endpoints and myocardial infarction in treated patients. However, the design of this study has been criticised, mainly for failure to measure oxidative stress and vitamin E levels in most of the patients [16-18] and because the study had a small sample size with resultant wide confidence intervals for a broad composite endpoint [19,20]. The authors responded but only reported vitamin E and oxidative stress measures in 15 patients from each group [21].

A recognised weakness of many of the large vitamin E cardiovascular trials is a lack of oxidative stress data assessing whether the supplementation was pharmacologically effective. In addition there has been evidence from meta-analyses indicating potential safety concerns with higher doses of alpha tocopherol [22].

Roberts et al (2007) conducted a time course and dose determining study in hypercholesterolemic patients. They reported that 1600 IU of alpha tocopherol was required over 16 weeks to significantly reduce plasma F_2_-isoprostanes, a biomarker of oxidative stress [23]. No such data is available for haemodialysis patients. Hence, this study has been designed using this approach to establish a dose of alpha tocopherol that will achieve a significant reduction in oxidative stress, and to determine how long it would need to be administered for, to achieve this effect. This information will be used to plan a large, randomised controlled trial to assess the effects of alpha tocopherol on cardiovascular outcomes in haemodialysis patients.

## Methods

### Design and Setting

This investigation will involve two sequential components, a time course, followed by a dose response study. The studies will be conducted at the Renal Medicine Department of the Royal Brisbane and Women's Hospital, Brisbane, Australia, which services a population of approximately 1.2 million people.

### Ethical Considerations

The Royal Brisbane and Women's Hospital Research and Ethics Committee approved the studies. The Ethics Committee will promptly receive all adverse event reports along with a final report.

### Eligibility

For both studies, inclusion criteria are; age > 18 and < 85 years, incident and prevalent dialysis patients, who are undergoing regular three times per week, hospital based haemodialysis and who have elevated oxidative stress. Elevated oxidative stress will be defined as having total plasma F_2_-isoprostane levels > 500 pg/mL. This is based on a study that compared plasma F_2_-isoprostane levels in chronic haemodialysis patients (1662 ± 289 pg/mL) with matched healthy controls (396 ± 18 pg/mL) [24,25] and the Roberts et al. (2007) study that defined elevated oxidative stress as two standard deviations above the mean [23].

Patients will be excluded if they are currently taking alpha tocopherol or have been taking it in the previous three months for at least one week, and if they are unable, or unwilling to give informed consent. In addition, patients who are participating in another investigational study, or are within 30 days of completing an investigational study, or patients who are taking warfarin, desimpramine, chlorpromazine and chloroquine will also be ineligible.

### Identification of Eligible Patients

Eligible patients will be screened from the haemodialysis unit and will receive a copy of the patient information and consent form. An investigator will then explain the study during a clinical consultation. The patient will then be asked to take the information and consent form away with them and make a decision before their next haemodialysis visit. If they agree to participate, they will sign the consent form with an independent person signing as a witness.

### Randomization

An individual not associated with the trial will perform the randomization for both studies using a computer generated random number system.

### Time-course study

Twenty participants will be recruited for the time-course study with ten randomly allocated to a treatment group and ten to a placebo group. Both groups will be required to take two capsules per day (one in the morning and one at night) each containing either a placebo or 800 IU of natural (RRR) alpha tocopherol (total 1600 IU/day) for 20 weeks.

### Dose-response study

Following the time course study, sixty participants will be recruited for the dose-response study with placebo, 100 IU/day, 200 IU/day, 400 IU/day, 800 IU/day and 1600 IU/day natural (RRR) alpha tocopherol groups each consisting of ten people. If patients from the time course study agree to participate in the dose-response study they will undergo a 12-week period (wash out) where they will not be consuming alpha tocopherol. Dose-response study participants will be required to take two capsules per day (one in the morning and one at night) containing either a placebo or alpha tocopherol, to provide the respective IU/day doses.

The placebo will contain the emulsifying agent (wheatgerm oil) used in the alpha tocopherol supplement. Cognis Nutrition & Health Pty Ltd, Sydney, Australia, will supply all capsules.

### Blinding and concealment

All vitamin E and placebo capsules will be identical. The allocation will be provided coded to the person who dispenses the medication thus ensuring the dispenser and patient are blinded to the allocation.

### Adverse event monitoring

A medical co-investigator will assess whether reported adverse events are related to the study medication and will also assess all signs, symptoms and complaints. All adverse events, regardless of relationship to the study, will be recorded and will include; the specific condition or event and direction of change, whether the condition is pre-existing, the dates and times of the occurrence, the severity and significance to study, the action taken and the outcome.

Serious adverse events recorded will include death, in-patient hospitalisation, persistent or significant disability or incapacity, cancer, or be life threatening. Additionally, important medical events that may not result in the above stated outcomes but may require medical or surgical intervention will also be reported.

### Primary Objectives and Outcome Measures

The first primary objective is to determine the time point when oxidative stress is significantly reduced in haemodialysis patients taking 1600 IU/day of alpha tocopherol. Based on the Roberts et al. (2007) study in hypercholesterolemic patients, it is hypothesised that this will occur at 16-weeks [23].

Using this information, the second primary objective is to determine the optimal dose of alpha tocopherol required to reduce oxidative stress in patients undergoing haemodialysis. Based on the SPACE trial, it is hypothesised that ≥ 800 IU of alpha tocopherol will be required to significantly reduce oxidative stress [15].

### Secondary Objectives and Outcome Measures

For both studies, secondary objectives will be to determine the effects of alpha tocopherol on additional measures of oxidative stress and antioxidant status. The additional measures will be plasma protein carbonyls, malondialdehyde and antioxidant enzyme activities of superoxide dismutase, glutathione peroxidase and catalase.

### Visit One (establishment of oxidative stress status)

After obtaining written, signed and witnessed informed consent patients will have blood taken from the dialysis line, at the start of dialysis, to measure total plasma F_2_-isoprostanes to assess their eligibility (> 500 pg/ml) to progress to the next phase of the study.

### Visit two

Once randomized, patients will be booked into a clinic appointment for baseline trial measures. This will occur on a mid-week dialysis day. At the first trial visit, additional data will be obtained from the medical records (medical history, medications) and measures of height, weight and blood pressure will be recorded. Additional blood will be collected pre-dialysis for routine blood chemistry and for measures of plasma F_2_-isoprostanes and alpha tocopherol.

### Time course study

Participants recruited into the time-course study will be required to consume 1600 IU of alpha tocopherol orally each day for 20 weeks or an identical placebo. Blood samples of 8 mL will be taken once every fortnight from the dialysis line, at the start of dialysis, during a normal mid-week dialysis visit and analysed for plasma F_2_-isoprostanes and alpha tocopherol.

### Dose-response study

Participants recruited for the dose-response study will be allocated after randomisation to consume either a placebo, 100 IU, 200 IU 400 IU, 800 IU or 1600 IU of alpha tocopherol orally each day for the duration determined by the time-course study. Blood samples of 8 mL will be taken at the completion of the time period from the dialysis line, at the start of dialysis, during their normal mid-week dialysis visit and analysed for plasma F_2_-isoprostanes and alpha tocopherol

### Adherence to Therapy

Patients will be required to return the container each month with unused capsules inside. Adherence to therapy will be assessed by duplicate table counts of the remaining capsules conducted independently by two study investigators.

### Withdrawal from Study

Patients will be withdrawn from the study at their request, without prejudice, as documented and explained at the time of consenting. Patients who withdraw will be invited to consent to follow-up testing for the remainder of the trial to enable an intention to treat data analysis.

### Blood collection, separation and storage

EDTA blood (approx. 8 mL) will be collected from the sample line shortly after the patient has commenced dialysis. If there is considerable time (> 10 mins) between blood collection and separation then the blood sample will be placed on ice. Centrifugation will be at 600 × g for 10 mins with plasma aliquots then stored at -80°C.

### F_2_-isoprostanes

Total isoprostanes (8-iso-PGF_2α_) will be extracted from plasma according to a modified method of Taylor and colleagues [26]. Samples from the freezer will be thawed on ice then diluted with distilled water and spiked with an internal standard; 8-iso-PGF_2α_-d_4 _(Cayman chemical, Michigan, USA) before methanolic NaOH solution is added. The solution will be vortexed, caped and placed in a water bath at 37°C for 60 min. This is followed by further dilution with distilled water and then acidification to pH 3 with hydrochloric acid before being extracted with hexane. Following gentle rotation and centrifugation at 3000 × *g*, hexane extracts will be removed and discarded. The aqueous layer will then be extracted twice with ethyl acetate, with extracts pooled and dried under nitrogen. Once dry, the samples will be reconstituted with acetonitrile, vortexed and transferred into 300 μL glass inserts and dried ready for derivatisation. The derivatization method will be based on that used by Mori and colleagues [27]. To the dried extract, pentafluorobenzylbromide and 20 μL diisopropylethylamine will be added and incubated at room temperature for 30 min. Following incubation, samples will be further dried under nitrogen to give the F_2_-isoprostane pentafluorobenzyl ester. Samples will then be treated with pyridine, bis(trimethylsilyl)trifluoroacetamide and trimethylchlorosilane and incubated at 45°C for 20 min to yield the trimethylsilylethers. After incubation, hexane will be added to each sample, mixed and placed in the auto sampler. Samples will then be analyzed using a Varian 320 MS/MS with a Varian 450 gas chromatograph using Varian MS Workstation - system control software version 6.9.1 (Varian, Australia). Using a 10 μL Hamilton syringe with 1.2 μL of sample injected for each analysis. The injector will operate at 250°C with a Varian FactorFour Capillary Column - VF - 5 ms 30 m × 0.25 mm ID DF = 0.25 using helium as the carrier gas at a flow rate of 1.0 ml·min^-1 ^with pressure maintained at 13.9 psi. The column oven will start at 160°C held for one minute then increase to 300°C over 7 min then holding for 10 min for an overall run time of 18 min with the peaks eluting around 10.3 min. Running in negative chemical ionization mode the reagent gas will be methane with an ion source pressure of 7.00 Torr and argon as the collision gas at a pressure of 2.00 mTorr. The mass size of our compounds is expected to be 569 and 573 for isoprostanes and the internal standard, respectively.

### Alpha tocopherol

Plasma alpha tocopherol levels will analysed using a modified HPLC method from Katsandinis et al. [28]. Plasma aliquots will be thawed on ice and mixed with ethanol/BHT and vortexed. Hexane will then be added and samples gently mixed for 10 mins before being centrifuged at 4,000 × g for 10 mins. The hexane layer will be removed, dried and reconstituted with mobile phase containing hexane and isopropanol. Vitamin E concentrations will be measured at 295 nm using HPLC (Shimazu) with a LiChrospher C18 column (250 × 4 mm, 5 μm, 1 ml/min flow rate, 9 MPa backpressure).

### Sample Size Calculation

The primary outcome measure for both studies will be the total plasma F_2_-isoprostane levels. For both studies, we will assume that the initial plasma F_2_-isoprostane levels will be 1600 ± 300 pg/mL. This is based on the inclusion criteria requiring patients to have plasma F_2_-isoprostane levels > 500 pg/mL, and also data showing plasma F_2_-isoprostane levels in haemodialysis patients were 1662 ± 289 pg/mL [24,25]. A decrease in plasma F_2_-isoprostane levels to 50% (800 pg/mL) of the initial values will be regarded as significant. To our knowledge, there is little data to support this assumption as no studies have assessed the relationships between plasma F_2 _isoprostanes and long-term health outcomes. Data from the Roberts et al. (2007) study found an approximately 50% reduction in plasma F_2_-isoprostane levels after 16 weeks vitamin E treatment in hypercholesterolemic patients [23]. With these assumptions, accepting their limitations and using a change variance of 350 pg/mL, with alpha = 0.05, beta = (1-0.1 = 0.9) we require five subjects per group. Assuming that five subjects per group will withdraw, die or receive a kidney transplant during the trial we will recruit ten subjects per group for both studies.

### Statistical Analyses

The analysis of both the time-course and dose-ranging study will focus on analysing the changes in the levels of plasma F_2_-isoprostanes and alpha tocopherol, which occur during the intervention. The time-course study will use general linear modelling to analyse the levels of plasma F_2_-isoprostanes at bi-weekly intervals and levels of alpha tocopherol will be compared at baseline and week 20. In the dose-ranging study we will use general linear modelling to compare the changes in plasma F_2_-isoprostane levels between the intervention and placebo group at baseline and at the completion of the study. All statistical analyses will be performed using STATA statistical software (STATA 10; Statistical data analysis; Stata Corp; College Station; Texas, USA).

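### Dose-response model compares changes in F2-isoprostanes and names no baseline covariate; adjusting for baseline would probably gain precision at almost no cost

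*Protocol article*

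**What the plan says.** The Statistical Analyses section of the protocol opens by saying that the analysis of both studies will centre on changes in F2-isoprostanes and alpha tocopherol. For the dose-response study it then says "we will use general linear modelling to compare the changes in plasma F_2_-isoprostane levels" between treated and placebo patients, start against end of treatment. For the time-course study the model is of F2-isoprostane levels at two-weekly visits. The section neither names baseline as a covariate nor rules it out.

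The Sample Size Calculation section states "we will assume that the initial plasma F_2_-isoprostane levels will be 1600 ± 300 pg/mL" and sets the target: "A decrease in plasma F_2_-isoprostane levels to 50% (800 pg/mL) of the initial values will be regarded as significant". The calculation is made "using a change variance of 350 pg/mL", and "with alpha = 0.05, beta = (1-0.1 = 0.9) we require five subjects per group". Ten per group are recruited to allow for five losses.

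Under Visit two, F2-isoprostanes are measured before treatment, so a baseline value exists for each randomised patient. The document gives no follow-up SD and no correlation between baseline and follow-up.

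**The concern.** A change score is a baseline-adjusted analysis with the slope on baseline fixed at 1. When the true slope is well below 1, subtracting the whole baseline adds noise. It also over-corrects for chance imbalance: an arm that happens to start high will appear to fall further. The plan's two planning figures, taken together, point to a low slope.

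The second primary objective is to find the optimal dose, and the stated hypothesis is that at least 800 IU is needed. With 5 to 10 patients per group, avoidable noise makes non-significant results at 100 to 400 IU more likely, and such results would be read as supporting that hypothesis. The dose for the planned outcomes trial is to be chosen from these data.

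**Working it through.** **Inputs from the Sample Size Calculation section.** Baseline SD s0 = 300 pg/mL; change SD 350 pg/mL; difference 800 pg/mL (1600 to 800, placebo change taken as 0); alpha 0.05, taken as two-sided; power 0.90. **Assumed, because it is not in the document:** follow-up SD s1 = 300 pg/mL, varied below.

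**1. The plan's own figure.** n = 2 × [350 × (1.960 + 1.282)/800]² = 4.02, rounded up to 5 per group, as stated. If 350 were a true variance, the SD would be √350 = 18.7 and n would be 1. So 350 is an SD.

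**2. Implied correlation.** Var(change) = s0² + s1² − 2ρ·s0·s1. With s1 = 300: 122,500 = 180,000 × (1 − ρ), so ρ = 0.319.

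**3. Residual variances.**
- Unadjusted change: 350² = 122,500.
- Follow-up value alone: 300² = 90,000. The change score has 122,500/90,000 = 1.36 times this variance.
- Baseline-adjusted: 90,000 × (1 − 0.319²) = 80,816, SD 284. Ratio to change: 80,816/122,500 = 0.66, a 34% cut. Against the follow-up value alone the cut is only 10%.

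**4. Sensitivity to the missing follow-up SD** (s0 = 300 and change SD = 350 held fixed; adjusted variance = s1²(1 − ρ²)).

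| Follow-up SD | Implied ρ | Adjusted SD | Cut against change |
|---|---|---|---|
| 200 | 0.06 | 200 | 67% |
| 250 | 0.20 | 245 | 51% |
| 300 | 0.32 | 284 | 34% |
| 350 | 0.43 | 316 | 18% |
| 400 | 0.53 | 339 | 6% |

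Above 350 pg/mL the change score is no longer noisier than the follow-up value. With the cited SD of 289 at both times, ρ = 0.27 and the cut is 37%.

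**5. Cost of estimating the slope.** Multiply the ratio by 1 + 1/(N − g − 2), with N patients in g groups, at equal SDs of 300:
- N = 60, g = 6: 0.660 × 1.019 = 0.672, a 33% cut
- N = 30, g = 6: 0.660 × 1.045 = 0.690, a 31% cut
- N = 20, g = 2: 0.660 × 1.0625 = 0.701, a 30% cut
- N = 10, g = 2: 0.660 × 1.167 = 0.770, a 23% cut

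**6. Power, two arms, two-sided 5%, noncentral t.** For change, the noncentrality is δ/(350·√(2/n)) with 2n − 2 degrees of freedom. For the adjusted analysis it is δ/(284·√((2/n)(1 + 1/(2n − 4)))) with 2n − 3.

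| Difference δ (pg/mL) | n per arm | Change | Adjusted |
|---|---|---|---|
| 800 (planned) | 5 | 88% | 94% |
| 800 (planned) | 10 | 99.8% | about 100% |
| 400 (assumed) | 5 | 36% | 43% |
| 400 (assumed) | 10 | 68% | 82% |

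The 88% falls below the planned 90% because the t distribution is used; the normal approximation gives 95%. With the error pooled over six groups, power goes from 93% to 99% (800 pg/mL, 5 per group) and from 71% to 86% (400 pg/mL, 10 per group).

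**7. Chance imbalance.** At equal SDs, an arm that starts d higher shows an extra apparent fall of (1 − 0.319)·d under an unadjusted change. With 5 per arm, one standard error of the baseline difference is 300 × √(2/5) = 190 pg/mL, which gives 0.681 × 190 = 129 pg/mL.

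**The case against.** Comparing change from baseline between randomised arms is valid and conventional, and several stronger readings go further than the document allows.

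- **That the plan commits to an unadjusted change score.** A reader might infer this, but the text does not say it. A general linear model of change can include baseline, and the treatment estimate is then identical to that from modelling the follow-up value. A full protocol or analysis plan, not shown, may specify it. This stands. What remains is that the article does fix change as the response and sizes both studies on a change SD, without naming the covariate that would make that choice efficient.
- **That the plan's own SDs prove change is the noisier measure.** They do not. The 300 pg/mL is for initial levels only. If treatment halved every value, the treated follow-up SD would be nearer 150, and the same equation gives ρ = (90,000 + 22,500 − 122,500)/90,000 = −0.11. The back-calculated correlation is therefore fragile. The direction of the advice is not: change is adjustment with the slope forced to 1, so apart from the cost of estimating the slope, adjustment cannot have the larger residual variance.
- **That the gain is a free third everywhere.** The net gain is smaller in a small two-arm comparison. With 5 per arm at 800 pg/mL, using the follow-up value alone would do as well (96% against 94%).
- **That every time-course contrast also loses power.** That study's model is of levels, so this does not follow.
- **That the large power gains apply to the planned effect.** They arise at 400 pg/mL, a difference the plan does not state.
- **That a log-scale analysis is needed because the target is proportional.** No calculation here supports that as a requirement.

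**Conclusion.** The point holds for the dose-response study as a matter of efficiency. The protocol makes change the response and names no baseline covariate. If the follow-up SD is close to the baseline SD of 300 pg/mL, adjustment removes about a third of the residual variance across six groups, net of its cost.

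At the planned effect the benefit is modest: about six percentage points of power with 5 evaluable per arm, and negligible with 10. It matters more for smaller effects, such as might occur at the lower doses. The size rests on reading 350 pg/mL as an SD, which the stated sample size supports, and on the assumed follow-up SD, which the document does not give. The planned comparison is not invalid.

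**What to change.** In Statistical Analyses:

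- State that the dose-response general linear model includes each patient's baseline F2-isoprostane level as a covariate. The response may be follow-up or change, since the treatment estimate is the same.
- Add baseline as a covariate in the time-course model, with the post-baseline levels as responses.

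In Sample Size Calculation, label 350 pg/mL as the SD of change.

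The cost is a sentence for each model, one word in the sample-size text, and one degree of freedom per model. No extra data are needed. A log-scale analysis giving a ratio to placebo is optional and not part of this fix.

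### The dose-response analysis compares changes from baseline without naming baseline adjustment; on the plan's own SDs, using the baseline and screening readings as covariates would cut residual variance by about a third

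*Protocol article*

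**What the plan says.** For the dose-response study, the Statistical Analyses section relies on a general linear model whose purpose it describes as follows: "compare the changes in plasma F_2_-isoprostane levels between the intervention and placebo group at baseline and at the completion of the study". It mentions no adjustment for the baseline level.

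F2-isoprostanes are assayed twice before treatment. Visit One takes blood "to measure total plasma F_2_-isoprostanes to assess their eligibility (> 500 pg/ml"), and Visit two takes further blood "for measures of plasma F_2_-isoprostanes and alpha tocopherol". No section uses the Visit One value for anything except entry.

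The Sample Size Calculation assumes that "initial plasma F_2_-isoprostane levels will be 1600 ± 300 pg/mL" and proceeds "using a change variance of 350 pg/mL". It sets the target with the statement that "A decrease in plasma F_2_-isoprostane levels to 50% (800 pg/mL) of the initial values will be regarded as significant", and concludes "with alpha = 0.05, beta = (1-0.1 = 0.9) we require five subjects per group". Ten are recruited per group because five are expected to be lost.

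The documents disagree on post-treatment sampling in the dose-response study. The Abstract states: "Blood will be collected at baseline and every two weeks and analysed for plasma F_2_-isoprostanes and alpha tocopherol". The Dose-response study section that follows Visit two schedules blood at completion only.

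**The concern.** A change score subtracts the whole of the baseline reading from the completion reading. When the two are only weakly correlated, the subtraction adds more noise than it removes. The plan's own planning figures point to a weak correlation, and the analysis as written does not guard against it.

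The second primary objective is to find the dose needed to lower oxidative stress. That turns on whether each dose separates from placebo with ten patients per arm recruited and perhaps five completing. At lower doses, where the effect may be below the planned 800 pg/mL, avoidable noise could make a working dose look inactive. The result is meant to inform a large outcome trial.

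**Working it through.** **Inputs (Sample Size Calculation).** Single-reading SD 300; 350 pg/mL for the change; target difference 800; alpha 0.05, taken as two-sided because sidedness is not stated; power 0.90; five per group.

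**Reproducing the stated sample size.** The 350 is called a variance but carries the unit pg/mL. Taken as an SD, with the two-sided normal approximation:

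n = 2 × [350 × (1.960 + 1.282) / 800]² = 4.02, rounded up to 5.

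This matches the plan. Taken literally as a variance (SD 18.7), it would give 1 or 2 per group. So 350 was used as an SD.

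**Implied correlation.** With equal pre and post SDs, Var(change) = 2 × 300² × (1 − r):

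- 122,500 = 180,000 × (1 − r), so r = 0.319.
- Shared (between-patient) variance = 0.319 × 90,000 = 28,750. The remainder is 350²/2 = 61,250.

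**Variance of each patient's contribution to an arm comparison.**

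- Unadjusted change: 350² = 122,500.
- Completion value alone: 300² = 90,000.
- Change from the mean of the two pre-treatment readings: 61,250 × (1/2 + 1) = 91,875, no better than the completion value alone.
- Completion value adjusted for the visit-two baseline: 90,000 × (1 − 0.319²) = 80,816. Reduction: 1 − 80,816/122,500 = 34%.
- Completion value adjusted for both pre-treatment readings, taken as equally informative: the mean of the two has variance 28,750 + 61,250/2 = 59,375, so the residual is 90,000 − 28,750²/59,375 = 76,079. Reduction: 1 − 76,079/122,500 = 38%.
- What the screening reading adds to a baseline-adjusted model: 1 − 76,079/80,816 = 6%.

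Most of the gain therefore comes from adjusting for baseline.

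**Two-group power.** Noncentral t, noncentrality = difference / √(2V/n), df = 2n − 2 less one per covariate.

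- 800 pg/mL, five per arm: 0.88 for the change score; 0.97 with one covariate; 0.97 with both.
- 400 pg/mL (assumed, a 25% fall), ten per arm: 0.68 for the change score; 0.84 with one covariate; 0.86 with both.
- 800 pg/mL, ten per arm: already 0.998 for the change score.

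The adjusted figures are slightly optimistic for a two-arm fit, because they ignore chance covariate imbalance between small arms.

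**Sensitivity.** The size of the gain depends on the equal-SD, common-response model.

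- True response varies between patients (assumed SD 100 to 200, independent of the starting level, change SD still 350). With SD 100, the remainder is (122,500 − 10,000)/2 = 56,250, the shared part 33,750 and the completion variance 100,000. The residual with one covariate is 100,000 − 33,750²/90,000 = 87,344, 29% below the change score. With SD 200 the same steps give 130,000 − 48,750²/90,000 = 103,594, 15% below.
- Post SD of 250 with change SD 350: r = (300² + 250² − 350²)/(2 × 300 × 250) = 0.20. The residual is 250² × (1 − 0.20²) = 60,000, 51% below.
- Post SD of 150, as a proportional halving would give: r = −0.11, so the variance split above no longer applies.

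**Selection.** Under mean 1600 and SD 300, the chance of a reading below 500 is about 0.0001. Truncation hardly distorts the screening value, and it occurs before randomisation, so it affects the arms alike.

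**The case against.** The strongest reply is that nothing here is an error. Comparing changes from baseline is valid and conventional, general linear modelling permits a baseline covariate, and an article may leave covariates to the analysis plan. This stands as far as validity goes: the point is a gain in efficiency, not a correction of bias. But the section does fix the comparison as one of changes and names no adjustment, so a reader following it would run the noisier analysis.

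Four stronger readings are tempting, and the document does not support them.

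- *That 25% to 50% of the variance could be removed simply by averaging readings already taken.* The 25% is measured against an unadjusted change score, and the result (91,875) is no better than ignoring baseline. The 50% needs a second end-of-treatment sample, which the Abstract implies and the Methods do not schedule. Averaging the last two visits could also understate an effect still developing.
- *That the plan shows two-thirds of a reading to be within-patient noise.* The ratio 61,250/90,000 = 68% requires equal pre and post SDs and no variation in response. The plan states neither and gives no source for 350. With response SD of 100 to 200 the share falls to 63% to 46%.
- *That both studies are affected.* The time-course study models fortnightly levels.
- *That the trial is underpowered for its target because of this.* With ten completers at 800 pg/mL, power is already about 0.998. The gain matters at five completers or for smaller effects.

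Two practical objections also hold. The Visit One sample is not tied to a mid-week session, unlike the later ones, so it may be less informative than assumed. And patients re-entering from the time-course study have no stated re-screen after washout, so their Visit One reading could predate 20 weeks of treatment.

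**Conclusion.** The point holds for the dose-response study as an inexpensive improvement. An adjusted analysis chooses the weight on baseline from the data. The change score fixes that weight at one and the completion value alone fixes it at zero, so apart from the small cost of estimating the weight, adjustment cannot do worse than either.

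On the plan's figures, residual variance falls by 34% with the baseline as covariate and by 38% with both pre-treatment readings. These sizes rest on 300 and 350 being SDs, equal pre and post SDs, no variation in response, and a screening reading as informative as the baseline one. The 350-as-SD reading is well supported, because it reproduces the stated five per group; the other assumptions are not checkable from the document. The direction is more secure than the amount.

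The screening value is a minor addition. In a two-arm fit with five completers per arm its 6% is offset by the lost degree of freedom.

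The conflict between the Abstract and the Methods on dose-response sampling is a separate defect that must be reconciled.

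**What to change.** In Statistical Analyses, for the dose-response study, state that the completion F2-isoprostane value will be modelled by arm with the visit-two baseline and the visit-one screening value as separate covariates, in the same way for all arms. Separate covariates are preferable to their mean because the draw conditions may differ. Change may stay as the outcome, since the adjusted arm contrasts are identical once baseline is in the model.

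For patients who re-enter from the time-course study, use only a screening reading taken after the washout, and say what is done if there is none. Using the baseline alone for everyone would be an acceptable simplification that gives up about 6%.

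Fitting one model to all six arms keeps the cost low: with five completers per arm, residual degrees of freedom go from 30 − 6 = 24 to 22, against 8 to 6 in a two-arm fit. No additional patient, sample or assay is needed.

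Separately, reconcile the fortnightly dose-response sampling in the Abstract with the completion-only sampling in the Methods. Until then, claim no benefit from averaging end-of-treatment samples.
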